### Sample size and power analysis

A clinically meaningful difference was defined as a reduction of 16% or more in the number of BPD symptoms, according to the MSI-BPD. This estimate is informed by previous studies using this measure, clinical judgement and existing trials examining shortened skills-based interventions for BPD [21, 22]. For this trial, the difference to be detected was calculated using the mean baseline MSI-BPD score (8.16) and standard deviation (2.08) in Miller et al. [22]. The reduction of 16% represents the within-subject mean symptom reduction at the end of the 16-week treatment block, relative to the individual’s baseline. Thus, based on a power of 80%, an alpha level of .05, the total number of participants required in each group is 40. However, accounting for a drop-out rate of 30%, 58 participants will need to be recruited for each group (N = 116).

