#### Primary analyses

The effect of treatment on primary outcomes will be evaluated using a linear mixed models approach, to account for the repeated measured structure of the data (SPSS-25). The data will be analysed as an intention-to-treat with time as a repeated measure. Recommended as the gold standard for study designs of this nature, this design (i) allows for the assessment of individual trends over time, with sensitivity to detect change; (ii) takes into account the longitudinal nature, utilising all data available; and (iii) controls for any pre-intervention differences [9, 27]. A linear mixed models analysis will be performed for each primary outcome variable symptom reduction (total number of BPD symptoms measured by the MSI-BPD) and service utilisation (inpatient hospital admissions and emergency department presentations). Change over time on these variables will be modelled as a within-subject effect of time, and the effectiveness of the intervention conditions will be determined by significant two-way group × time interaction. Although the change between baseline and end of the 16-week treatment block is of primary interest, three time points will be included to also examine the change during treatment and whether any changes are maintained following treatment. Within- and between-group effect sizes will be calculated, compared and interpreted according to the Cohen [5] recommendations.

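### The 80% power claimed for the group × time test on MSI-BPD rests on an unstated baseline-to-follow-up correlation of about 0.5 or more; adjusting for baseline would remove most of that dependence at no cost in patients

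*Protocol article*

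**What the plan says.** Under Sample size and power analysis, the protocol article sets the target effect: "A clinically meaningful difference was defined as a reduction of 16% or more in the number of BPD symptoms" on the MSI-BPD. It continues that "the difference to be detected was calculated using the mean baseline MSI-BPD score (8.16) and standard deviation (2.08"), both figures from an earlier study. The 16% is described in terms of change: "The reduction of 16% represents the within-subject mean symptom reduction at the end of the 16-week treatment block". The stated result, "based on a power of 80%, an alpha level of .05", is that "the total number of participants required in each group is 40", raised to 58 for 30% drop-out. The section names no test and gives neither an SD of change nor a correlation between baseline and follow-up.

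Under Primary analyses, MSI-BPD goes into a linear mixed model with time as a repeated measure, and "the effectiveness of the intervention conditions will be determined by significant two-way group × time interaction". Baseline to the end of the 16-week block is the comparison of main interest, with three time points in the model. The section says that the approach "controls for any pre-intervention differences", but specifies neither a baseline covariate nor a constraint on the baseline means.

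**The concern.** When baseline is one of the repeated outcomes and the arms are free to differ there, the group × time term for baseline to end of treatment is the difference between arms in mean change. Its precision depends on the SD of change, not on the spread of scores at one visit. The two are equal only at r = 0.5, and below that the SD of change is larger. The only SD in the sample size section is a baseline one, so the stated 80% is tied to the planned test through a value of r that nobody has written down.

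The contrast also subtracts the whole of any chance baseline difference, which amounts to fixing the regression slope at 1. With equal SDs and r below 1 this over-corrects. The trial could therefore miss the difference it was sized for because of the form of the contrast alone, although a more precise estimate is available from scores it already collects.

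**Working it through.** **Inputs from the protocol article.** Baseline mean 8.16, SD 2.08, reduction 16%, power 80%, alpha .05, 40 per group before drop-out, drop-out 30%, allocation 1:1. **Assumptions.** Two-sided test; r over a range; the same SD at both times unless stated; 1.31 points taken as the between-arm difference.

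**1. The plan's own figure.**
- Difference: 0.16 × 8.16 = 1.3056. Standardised: 1.3056 / 2.08 = 0.628.
- Two-sample normal approximation: n = 2 × (1.960 + 0.842)² / 0.628² = 39.8, so 40 per group.
- Drop-out: 40 / 0.7 = 57.1, so 58.

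The 40 and the 58 both reproduce. The same 39.8 also results if 2.08 is taken as an SD of change in a two-sample test (which means r = 0.5), or from a one-sample paired calculation at r = 0, where the SD of change is 2.08 × √2. The test behind the 40 is therefore inferred. Under none of these readings is r stated or justified.

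**2. The planned contrast and the baseline-adjusted one.**
- Change: SD = 2.08 × √(2(1 − r)).
- Baseline-adjusted: SD = 2.08 × √(1 − r²).
- Variance ratio, adjusted to change: (1 − r²) / (2(1 − r)) = (1 + r)/2. The adjusted variance is 35% lower at r = 0.3 and 25% lower at r = 0.5.

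**3. Power with 40 evaluable per group (noncentral t).**

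| r | SD of change | Power, change | SD adjusted | Power, adjusted |
|---|---|---|---|---|
| 0 | 2.94 | 50% | 2.08 | 79% |
| 0.2 | 2.63 | 59% | 2.04 | 81% |
| 0.3 | 2.46 | 65% | 1.98 | 83% |
| 0.4 | 2.28 | 72% | 1.91 | 86% |
| 0.5 | 2.08 | 79% | 1.80 | 89% |
| 0.6 | 1.86 | 87% | 1.66 | 93% |

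The 79% entries (change at r = 0.5, adjusted at r = 0) differ from 80% only because t replaces the normal approximation, which gives 80.2%. On the normal approximation the change contrast reaches 80% at r = 0.498. It would need 64, 56 or 48 per group at r = 0.2, 0.3 or 0.4.

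**4. Follow-up SD 20% larger (assumption).**
- Change SD = 2.08 × √(1 + 1.44 − 2.4r): 2.73 at r = 0.3 and 2.32 at r = 0.5, giving 56% and 70% power.
- Adjusted SD = 2.08 × 1.2 × √(1 − r²): 2.38 and 2.16, giving 68% and 76%.

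With unequal SDs, write s₀ for the baseline SD and s₁ for the follow-up SD. Change variance minus adjusted variance is then (s₀ − r·s₁)², which is never negative.

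**The case against.** A reader might infer that the trial is underpowered. The documents do not show that. They give no r, and at r of about 0.5 or more the plan meets its target. Some features could lower r: every participant must meet the diagnosis at entry, the 16-week block ends at week 36, and care in the usual-treatment arm is not controlled. These are reasons not to take 0.5 for granted, not evidence of a lower value.

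A reader might also infer that the 40 certainly came from a comparison of scores at a single visit. That is not established, since other readings give the same number and the section describes the 16% in the language of change.

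Recruitment helps a little. Trial status reports 125 recruited. With 30% drop-out that leaves 125 × 0.7 / 2 = 43.75 per group, and the break-even r falls to about 0.45. The dependency is weaker but remains.

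The strongest point is that the wording does not exclude a common-baseline model, where the effect is also read from group × time terms, and that such detail often sits in an analysis plan. The difficulty is that the article fixes the interaction as the criterion and claims control of baseline differences without naming anything beyond differencing. Minimisation does not supply that control either, because MSI-BPD is not among its factors. Both contrasts are unbiased in a randomised trial, so what remains is precision and a power statement that needs its condition.

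Finally, Table 1 lists MSI-BPD under Randomisation. Participant randomisation together with Baseline and follow-up evaluation indicates that the diagnostic score precedes allocation. In a non-blind trial this should be confirmed before the score is used for adjustment.

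**Conclusion.** The point holds as an unstated dependency with a free remedy. For the contrast of main interest, 40 per group gives the stated 80% only if r is about 0.5 or more. Baseline adjustment is at least as precise at any r, and with equal SDs it stays at about 79% or above from r = 0 upwards.

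It would be too strong to say that adjustment guarantees 80%: that needs a follow-up SD close to 2.08. With a follow-up SD 20% larger the adjusted analysis falls short for r = 0.3 to 0.5, though by less than the change contrast.

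The figures rest on 1.31 points being the between-arm difference, whereas the article describes the 16% as a within-subject reduction; that is a separate question. They apply to the single baseline-to-end contrast, not to an overall interaction test across three time points.

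**What to change.** Under Primary analyses, for MSI-BPD, specify one of two models:
- a mixed model for the post-baseline scores with group, time, group × time, baseline MSI-BPD and baseline × time as fixed effects; or
- a longitudinal model that constrains the arms to a common baseline mean.

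Read the effect as the adjusted group difference at the end of the 16-week block. First confirm that the baseline MSI-BPD is taken before allocation, and align Table 1 with the text.

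Under Sample size and power analysis, state that 2.08 is a baseline SD and that the 80% applies to the baseline-adjusted comparison provided the follow-up SD is similar.

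The cost is wording and one model specification, with no added patients, visits or data, and N is unchanged. With the covariate form, participants without any post-baseline score leave the model, although they carry no information on the treatment effect; the common-baseline form keeps them.

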### Baseline and follow-up evaluation

The McLean Screening Instrument for Borderline Personality Disorder ((MSI-BPD) [32] and the SCID-5-PD will be conducted at baseline for diagnosis. Evaluation will take place at the completion of the 12-week and 16-week interventions and 16 weeks following the end of treatment to assess the change in BPD symptom using the MSI-BPD. All participants will be contacted for assessment at these time points regardless of treatment arm or continuation in treatment.

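### The effectiveness rule for MSI-BPD is the overall group × time interaction, not the baseline-to-end-of-block contrast that the plan calls primary and sized the trial on

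*Protocol article*

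**What the plan says.** In the protocol article, Data analysis plan, Primary analyses, each primary outcome is analysed with a linear mixed model, and the decision rule is explicit: "the effectiveness of the intervention conditions will be determined by significant two-way group × time interaction". The next sentence reads "Although the change between baseline and end of the 16-week treatment block is of primary interest, three time points will be included". It explains that the extra time points serve to look at the course during treatment and at maintenance.

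Sample size and power analysis ties the target effect to the same time point: "The reduction of 16% represents the within-subject mean symptom reduction at the end of the 16-week treatment block". The target is 16% of a baseline mean of 8.16, with SD 2.08, and the calculation is "based on a power of 80%, an alpha level of .05".

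The article does not name the three time points in the model. Baseline and follow-up evaluation lists three assessments after baseline: "Evaluation will take place at the completion of the 12-week and 16-week interventions and 16 weeks following the end of treatment". Table 1 places the end of the 16-week group programme at week 36 and the follow-up at week 52. The article does not say whether time is categorical or continuous.

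**The concern.** The plan attaches one conclusion, effectiveness, to a test that is not the test of the effect it calls primary. An interaction over all modelled time points asks whether the arms' profiles differ anywhere. The effect of primary interest is a single difference: how much more one arm changes than the other between baseline and the end of the 16-week block. No sentence makes that single difference decisive, or even a condition for the claim.

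Followed as written, the rule could yield a claim of effectiveness when the arms are equal at the end of the block and differ only at another visit. Equally, a reader given only the interaction p-value could not tell at which visit the arms differ. Once results are known, a team could argue from either sentence, because one names the interaction and the other names the contrast.

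**Working it through.** **1. The plan's own figure.** Target difference: δ = 0.16 × 8.16 = 1.3056 points. Standardised: 1.3056 / 2.08 = 0.628. For a two-sided two-sample comparison at 0.05 with 80% power, n per arm = 2 × [(1.960 + 0.842) × 2.08 / 1.3056]² = 39.84, rounded up to 40. With 30% dropout, 40 / 0.70 = 57.1, rounded up to 58, so N = 116. The stated figures reproduce exactly, as a comparison at one time point and not as an interaction test.

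**2. Assumptions for the illustration.** The documents give δ, the SD and 40 evaluable per arm. The following are assumed: SD 2.08 at every visit; time categorical; visits at baseline, week 36 (end of block) and week 52 (follow-up); correlation 0.5 of each later score with baseline; correlation r = 0.5 or 0.7 between the two later scores; complete data on 40 per arm.

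**3. The primary contrast (1 df).** With correlation 0.5, the SD of change is 2.08 × √(2 × (1 − 0.5)) = 2.08. The standard error of the between-arm difference is 2.08 × √(2/40) = 0.465. The noncentrality is 1.3056 / 0.465 = 2.81 on 78 df, so power is 79%. With no true difference at week 36 it is significant 5% of the time.

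**4. The overall interaction (2 df).** Each change difference has variance 2 × 2.08² / 40 = 0.2163, and under these assumptions the two change differences correlate at r. For true differences δ₁ (week 36) and δ₂ (week 52),

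λ = (δ₁² − 2rδ₁δ₂ + δ₂²) / [0.2163 × (1 − r²)],

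referred to a noncentral F on 2 and 77 df (5% critical value 3.115). For δ₁ = 0 and δ₂ = 1.3056, λ = 1.7046 / (0.2163 × 0.75) = 10.5 at r = 0.5, and 1.7046 / (0.2163 × 0.51) = 15.5 at r = 0.7.

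| Week-36 difference | Week-52 difference | Rule met, r = 0.5 | Rule met, r = 0.7 | Primary contrast significant |
|---|---|---|---|---|
| 0 | 0 | 5% | 5% | 5% |
| 0 | ¼ δ | 10% | 13% | 5% |
| 0 | ½ δ | 28% | 39% | 5% |
| 0 | δ | 82% | 94% | 5% |
| δ | δ | 82% | 77% | 79% |
| δ | ¾ δ | 73% | 69% | 79% |
| δ | ½ δ | 69% | 73% | 79% |
| δ | ¼ δ | 73% | 84% | 79% |
| δ | 0 | 82% | 94% | 79% |

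**5. Sensitivity to what the article leaves open.** All figures here are for no end-of-block difference and a full δ at one other visit.
- One common correlation of 0.3, 0.5 or 0.7 among all visits: the rule is met 67%, 82% or 97% of the time. In a simulation of 20,000 trials per correlation, the interaction was significant while the primary contrast was not in 62%, 77% and 92%.
- Four time points (3 df): 66%, 81% and 97% for the same correlations.
- Time linear in weeks (slope comparison, correlation 0.5, δ at week 52): 66%.

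**The case against.** The strongest reply is that the plan already names the contrast. The sentence after the rule states that "the change between baseline and end of the 16-week treatment block is of primary interest", and the other visits are there to add information. In a mixed model with categorical time, one group × time coefficient is exactly that contrast. The choice of coefficient could be left to a statistical analysis plan that is not shown, and the planned between-group effect sizes would show direction. It is true that the priority is stated. But the sentence explains why more visits enter the model; it does not amend the rule just given, and no other passage does. A later analysis plan that made the contrast decisive would depart from the published rule.

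Other parts of the reply stand and limit the point:
- Categorical time and the choice of visits are assumptions. The article's wording also fits a linear time effect, or three rather than two visits after baseline. None of these versions tests the primary contrast.
- The 82%/94% case is extreme: equal arms at the end of treatment, then the full target difference 16 weeks later. Nothing in the documents suggests this pattern. The smaller differences in the table give a fairer picture of the range.
- In those scenarios the arms do differ at week 52, so the interaction is not wrong as a statement about the profiles. It is wrong as evidence for the end-of-block effect.
- Lack of direction is not peculiar to the interaction. A two-sided contrast can also be significant in favour of treatment as usual; its estimate then shows which arm did better at the named time point.

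**Conclusion.** The point holds as a mismatch between the decision rule and the primary contrast. The rule fixed in Primary analyses can be met with no between-arm difference at the end of the 16-week block. Under the stated assumptions this happens in 10% to 94% of trials, as the week-52 difference runs from a quarter to all of 1.31 points, against 5% for the primary contrast. The percentages rest on correlations and visit choices that the documents do not give; the mismatch itself does not.

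Three stronger readings are tempting but unsupported. First, a reader might infer that type I error is inflated. It is not: with no difference at any visit the interaction keeps its 5% level. Second, a reader might infer that the rule costs power. With a true end-of-block effect its power is about 69% to 94%, below or above the 79% of the single contrast, depending on how much of the effect remains at follow-up and on the correlation. Third, a reader might infer that a separate week-52 difference test would settle Hypothesis 2. Objectives words that hypothesis as equivalence, and a significant or non-significant difference test does not establish equivalence.

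**What to change.** In Primary analyses, replace the effectiveness rule for MSI-BPD with wording such as: effectiveness on MSI-BPD is determined by one prespecified 1-df contrast from the mixed model, the between-arm difference in change from baseline to the end of the 16-week block, tested two-sided at 0.05 and reported with its estimate, direction and 95% confidence interval.

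State which visits enter the model and that time is categorical, so that the contrast is defined. Make the between-arm contrast at follow-up and the overall group × time interaction secondary. Do not present the week-52 difference test as establishing the equivalence worded in Hypothesis 2.

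The cost is a sentence or two of text. The model and data are unchanged and no participants are added. The change should be recorded before the outcome data are analysed, so that the choice of test cannot follow the results.

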**Methods:**

Participants seeking treatment at two community mental health services will be invited to participate. Randomised controlled trial assignment will be to either (i) group skills treatment or (ii) treatment as usual. Group treatment will be offered via a stepped-care pathway with participants initially attending a 12-week group with the option of a subsequent 16-week group. The criteria for inclusion in continuing treatment includes meeting > 4 BPD diagnostic criteria or severity on GAF (< 65) at the completion of the 12-week group. Data will be collected at baseline and at five follow-up time points over a 12-month period.

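### For MSI-BPD, effectiveness is decided by an overall group × time interaction, which can be significant with no effect at the end of the 16-week block, the stated primary time point

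*Protocol article*

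**What the plan says.** All references are to the Protocol article.

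- **Decision rule (Primary analyses).** A linear mixed model is fitted to each primary outcome, with time as a repeated measure. The rule reads "the effectiveness of the intervention conditions will be determined by significant two-way group" (the interaction of arm with time). No between-arm contrast at a named visit is given a deciding role.
- **Primary interest (same section).** "Although the change between baseline and end of the 16-week treatment block is of primary interest, three time points will be included". The extra points are there to look at change during treatment and at maintenance afterwards. The section does not say which three points are meant. It also says that the method "takes into account the longitudinal nature, utilising all data available".
- **Sample size (Sample size and power analysis).** The target effect is set in these words: "A clinically meaningful difference was defined as a reduction of 16% or more in the number of BPD symptoms, according to the MSI-BPD". The reduction is taken at the end of the 16-week block relative to baseline, "based on a power of 80%, an alpha level of .05".
- **Schedule (Baseline and follow-up evaluation).** MSI-BPD is taken at baseline, and then "Evaluation will take place at the completion of the 12-week and 16-week interventions and 16 weeks following the end of treatment". That is four occasions. The abstract says more generally: "Data will be collected at baseline and at five follow-up time points over a 12-month period".

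**The concern.** The stated primary interest and the sample size both point to one comparison: the difference between arms in change from baseline to the end of the 16-week block (week 36 in Table 1). The verdict comes from a different test. With time as a repeated measure, the interaction asks whether the arms differ in change at any modelled visit. It has 2 degrees of freedom with three time points in all, or 3 with baseline plus three. A difference that appears only at the end of the 12-week group, or only at follow-up, can make it significant.

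The trial could then report the stepped-care programme as effective on MSI-BPD when nothing was found at the time point it was designed around. In the other direction, a real benefit at that point can be tested with less power than the single contrast would have, depending on how the effect evolves afterwards.

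**Working it through.** **Inputs.** From Sample size and power analysis: baseline mean 8.16, SD 2.08, 16% reduction, alpha 0.05, power 80%, 40 per arm, 30% dropout. Assumed, because the document gives none: correlation r between visits of 0.3, 0.5 or 0.7, either exchangeable or AR(1), and the same SD at every visit.

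**1. The plan's own figure.** Difference d = 0.16 × 8.16 = 1.3056 points, which is 1.3056 / 2.08 = 0.628 SD. Two-sided, two-sample normal formula: n = 2 × (1.960 + 0.842)² × 2.08² / 1.3056² = 39.8, so 40 per arm. With dropout, 40 / 0.70 = 57.1, so 58 per arm and N = 116. Both figures reproduce. This is a calculation for a single comparison at one time point.

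**2. The two tests.** Let s = 2.08 and n = 40 per arm. Under exchangeable correlation, each between-arm difference in change from baseline has variance (2/n) × 2(1 − r)s², and two such differences have covariance (2/n) × (1 − r)s².

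- End-of-block contrast: 1 df, z = d / √[(2/n) × 2(1 − r)s²].
- Interaction with three time points: 2-df Wald test with noncentrality λ = n(d₁² − d₁d₂ + d₂²) / [3(1 − r)s²], where d₁ and d₂ are the true differences at the end of the block and at follow-up.

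**3. No effect at the end of the block, full effect at follow-up (d₁ = 0, d₂ = 1.3056).** At r = 0.5, λ = 40 × 1.7046 / (3 × 0.5 × 4.3264) = 10.51. The 5% critical value of chi-square on 2 df is 5.99, so the probability of significance is 0.835.

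| Probability of a significant result | r = 0.3 | r = 0.5 | r = 0.7 |
|---|---|---|---|
| Interaction, exchangeable | 69% | 84% | 97% |
| Interaction, AR(1) | 61% | 74% | 92% |
| End-of-block contrast | 5% | 5% | 5% |

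Using a noncentral F distribution instead of chi-square gives 67% / 82% / 97% and 60% / 72% / 91%. A simulation of 20,000 trials at exchangeable r = 0.5 gave 81% for the interaction and 4.9% for the contrast. In 77% of the simulated trials the interaction was significant and the contrast was not. With all four occasions in the model (3 df, noncentral F), an effect at one non-primary visit only gives 56% to 98% across the same correlations and structures.

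**4. No effect anywhere.** The simulated rejection rate of the interaction is 4.9%, so its nominal level holds.

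**5. Full effect at the end of the block (exchangeable r = 0.5, 2 df).** The contrast has 80% power. The power of the interaction depends on what happens at follow-up:

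| Effect at follow-up | λ | Interaction power |
|---|---|---|
| Fully sustained (1.31) | 10.51 | 83.5% |
| Half (0.65) | 7.88 | 71% |
| Gone (0) | 10.51 | 83.5% |

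Under AR(1), a sustained effect gives interaction power of 61% / 74% / 92% at r = 0.3 / 0.5 / 0.7, against 66% / 80% / 95% for the contrast.

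**6. Adjusting for baseline.** The contrast variance falls from (2/n) × 2(1 − r)s² to (2/n) × (1 − r²)s². At r = 0.5 the factor falls from 1.00 to 0.75, and power rises from 80% to 90%. At r = 0.3 it rises from 66% to 84%.

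**The case against.** The plan does name the change of primary interest, so a reader has a prespecified time point, and an analysis plan that is not shown might name a contrast there. That would settle a silence. Here, however, the protocol positively states that the interaction determines effectiveness, so an analysis plan that let a contrast decide would contradict it. Nor does fitting time as a linear trend rescue the rule. The interaction would then have one degree of freedom but would test a difference in slopes, which is not the change from baseline to the end of the block.

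The scenario in step 3 is stylised: exactly no effect at one visit and the full design effect at another. It shows what the rule permits, not what is likely.

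Several stronger conclusions are tempting, and the document does not support them:

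- **That the false-positive rate is inflated or N = 116 is wrong.** Under the complete null the interaction holds 5%, and the stated sample size reproduces.
- **That the interaction loses power in general.** The 71% is the lowest value for the 2-df case at exchangeable r = 0.5. A fully sustained or fully faded effect gives slightly more power than the contrast.
- **That collected MSI-BPD data will be dropped.** The three time points can be read as the three evaluations after baseline, which fits the claim to use all data. The five follow-ups in the abstract describe data collection in general and need not refer to MSI-BPD. What stands is an ambiguity.
- **That treating baseline as an outcome is an error.** Such a model is valid, and the text does not say whether baseline means are free or constrained. Adjustment is an efficiency gain.
- **That the problem covers both primary outcomes.** Service utilisation is collected in two windows, 16 weeks before recruitment and 16 weeks after treatment. With two windows the interaction already has one degree of freedom.

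**Conclusion.** The concern holds for MSI-BPD, as a mismatch between the rule that decides effectiveness and the time point that the plan calls primary and was sized on. With 40 per arm, SD 2.08, no effect at the end of the 16-week block and 1.31 points at follow-up only, the rule declares effectiveness about 69% to 97% of the time under exchangeable correlation of 0.3 to 0.7, and 61% to 92% under AR(1). The end-of-block contrast does so 5% of the time. These ranges rest on assumed correlations, constant variance and three time points in the model.

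The effect on power has no fixed direction. At exchangeable r = 0.5 with 2 df it runs from 71% to 83.5%, against 80% for the contrast. The undefined three time points are a secondary ambiguity that should be cleared up in the same edit. The change should be made, since the rule as written can support a conclusion about the primary time point that the data there do not.

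**What to change.** In Primary analyses:

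1. Name the primary MSI-BPD test as the one-degree-of-freedom, model-based difference between arms at the end of the 16-week block (week 36), from the repeated-measures model with categorical time.
2. List the MSI-BPD visits in the model, including all scheduled ones, and say whether the count of three includes baseline.
3. Make the overall group × time interaction and the contrasts at the end of the 12-week group and at follow-up secondary.
4. As an optional gain in precision, adjust for baseline MSI-BPD or constrain the baseline means to be equal between arms.

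The cost is a few sentences of analysis wording. No new data, visits or participants are needed. Because the trial is not blinded, the wording should be settled before outcomes are compared by arm.
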